### **Arm 3: Multi-modal Intervention:**

**Group Exercise/Supplemental Home Exercise:** This will be delivered identically to Arm 2. **Oral Nutritional Supplementation:** As piloted in our Virtual Frailty Rehab Study, the ONS (each serving) contains 225kcal, and 11-12 grams protein (Glucerna, Ensure). Abbott Nutrition has provided support to this study in relation to the Abbott products Ensure® and Glucerna®. Participants are advised to take this with a meal or within 3 hours of exercise on activity days. Participants will be provided with two ONS each day of the study. The research staff will schedule Arm 3 participants for an initial and post assessment appointment. Working in consultation with the study geriatricians and pharmacist, as required, the multi-modal arm assessment will include: 1) Reviewing the participants' relevant medical and medication history at the baseline assessment (using the medical and medication history form completed and collected by study personnel). **Nutrition review:** Conduct nutritional screening flow (developed by a consultant dietician) and review any questions, provide some additional counseling/coaching at follow-up visits. ONS will be provided to all participants unless contraindicated. **Medication review:** Review/update current medication list (baseline medical history form) and forward the list and medical history to the consultant study pharmacist. Prior to the medication review, we will also be requesting permission from the participant to contact their family physician and community pharmacist to receive their medication list. The Beers and START/STOPP criteria will be considered to provide

PROTOCOL

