**FRAILTY REHABILITATION: A COMMUNITY-BASED INTERVENTION TO PROMOTE HEALTHY AGING**

recommendations, via letters, to the participant's family physician and community pharmacist. Research staff will follow up with participants regarding their medication lists to determine whether the medication recommendations were implemented.

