|                    | Sarcopenia                                                                         | Sarcopenia screening : 5-Time Chair Stand Test (SPPB)[Baseline and 4-month]
Sarcopenia: SARC-F [Baseline and 4-month]
Muscle Mass : DXA † and MRI* [Baseline and 4-month]
† Additional outcome assessed in up to 75 individuals with sarcopenia
* Additional outcome assessed in up to 36 individuals with sarcopenia                                                                                                                                                                                                                                                                                                                                                                                              |
| Exploratory | Healthcare utilization
[Baseline and 4-months and additional 6-month follow-up] | Number of emergency room visits
Number of hospitalizations & length of stay
Institutionalization (to long-term care)
(measured during intervention phase and 6-months)                                                                                                                                                                                                                                                                                                                                                                                                                                                                                                                                                                                        |

**4.9. Participant Feedback:** We will provide all participants with a participation satisfaction survey designed to facilitate a conversation about individual motivators and barriers to participation and attitudes and behaviours surrounding the frailty rehabilitation program. Participant characteristics that will be collected include age, sex, gender [measured by the Physical Self-Attribute Questionnaire [57], chronic conditions, medication use (medication # [total, started, stopped], 25(OH)D vitamin D level (mmol/L), participation in other programs and sociodemographic descriptors. Adherence will be examined in sub-analyses.

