| Healthcare Use  and Medications and Supplements     |                          | X                                     | X                   | X                                        |
| Physical Measurements                               |                          | X                                     | X                   |                                          |
| Physical Function  and Muscle Strength  |                          | X                                     | X                   |                                          |
| Frailty                                             |                          | X                                     | X                   |                                          |
| Mobility  and Sarcopenia                |                          | X                                     | XX                  |                                          |
| Fear of Falling                                     |                          | X                                     | X                   |                                          |
| Barriers to Exercise and Transportation            |                          | X                                     |                     |                                          |
| Lab Blood Work                                                  |                          | X                                     | X                   |                                          |

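### In Arm 3 only, the medication list on the baseline form is updated after randomisation, and if the updated list feeds the medication counts, comparisons between arms can be biased in either direction

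*Protocol*

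**What the plan says.** Section 4.5 places baseline measures before randomisation and states that research assistants and the pharmacist are not blinded.

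Section 4.9 begins its list with "Participant characteristics that will be collected include age, sex, gender" and goes on to include "medication use (medication # [total, started, stopped". Appendix B has a row for healthcare use "and Medications and Supplements", marked at baseline, 4 months and the 6-month telephone follow-up, with no distinction by arm.

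Section 4.6 describes the medication review under Arm 3. The instruction is: "Review/update current medication list (baseline medical history form) and forward the list and medical history to the consultant study pharmacist". Before the review, staff also ask the participant's permission to "contact their family physician and community pharmacist to receive their medication list". After the recommendation letters, "Research staff will follow up with participants regarding their medication lists to determine whether the medication recommendations were implemented".

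The Arm 2 text has no medication step, and Arm 1 receives none of the Table 1 components.

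**The concern.** The list to be updated is the one on the baseline form. A step confined to Arm 3 cannot be taken until the arm is known, so the procedure lets a baseline record change after allocation, in one arm, in the hands of unblinded staff, and with sources that the other arms lack.

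Started and stopped are change measures, so they depend on comparing two lists. If the lists differ in completeness by arm or by time, a drug that the participant was taking all along can appear as started, or one still being taken can appear as stopped. Medication review is one of the components that separate Arm 3 from Arm 2, so readers will look at these counts to see whether prescribing changed. Once a baseline list has been overwritten, no later analysis can recover it.

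**Working it through.** **1. Which list comes from where**

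| | Arms 1 and 2 | Arm 3 |
|---|---|---|
| Baseline, before randomisation | Common collection (Appendix B) | Common collection (Appendix B) |
| After allocation | No medication-list step described | List on the baseline form updated; physician and pharmacy lists if permitted; later follow-up of the list |
| 4 months and 6-month call | Common collection (Appendix B) | Common collection (Appendix B) |
| List used for the counts | Not stated | Not stated |

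**2. Effect on the counts**

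The protocol gives no figure for medication counts, so there is none to reproduce. Let T be the true mean number of drugs at baseline, the same in expectation in each arm. Let D be the true net reduction in Arm 3 relative to control. Let u be the mean number of drugs per Arm 3 participant that the common form misses and the reconciliation recovers, averaged over everyone, including those who refuse permission. Assume that the common form misses u drugs in every arm at each time and that the true control change is 0. The control arm then shows T-u at both times, a change of 0.

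| Lists used in Arm 3 | Difference in change, Arm 3 minus control | Difference in 4-month total |
|---|---|---|
| Common form at both times | (T-D-u)-(T-u) = -D | -D |
| (a) Common baseline, reconciled 4-month list | (T-D)-(T-u) = -D+u | -D+u |
| (b) Overwritten baseline, common 4-month list | (T-D-u)-T = -D-u | -D |
| (c) Reconciled at both times | (T-D)-T = -D | -D+u |

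In (a) the u recovered drugs are counted as started. In (b) they are counted as stopped.

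**3. Illustration**

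Neither D nor u is in the documents. The assumed ranges are D = 0.5 to 1.0 and u = 0.25 to 1.5 drugs. The entries are differences in change.

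| D | u | (a) -D+u | (b) -D-u | (c) -D |
|---|---|---|---|---|
| 0.5 | 0.25 | -0.25 | -0.75 | -0.5 |
| 0.5 | 0.5 | 0.0 | -1.0 | -0.5 |
| 0.5 | 1.0 | +0.5 | -1.5 | -0.5 |
| 0.5 | 1.5 | +1.0 | -2.0 | -0.5 |
| 1.0 | 0.25 | -0.75 | -1.25 | -1.0 |
| 1.0 | 0.5 | -0.5 | -1.5 | -1.0 |
| 1.0 | 1.0 | 0.0 | -2.0 | -1.0 |
| 1.0 | 1.5 | +0.5 | -2.5 | -1.0 |

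Case (a) can also be set up from a share missing. Assume 6 to 10 drugs with 5 to 20% missing from the form and all of them recovered. Then u runs from 6 x 0.05 = 0.3 to 10 x 0.20 = 2.0. The apparent change runs from -1.0+0.3 = -0.7 to -0.5+2.0 = +1.5. With 8 drugs and 10% missing, a true -0.5 shows as -0.5+0.8 = +0.3.

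**4. Sample size**

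The SPPB calculation in Section 5.0 (difference 1, SD 2, alpha 0.05 taken as two-sided, power 90%) needs 86 per arm by the t-test. Then 86/0.8 = 107.5, rounded up to 108 per arm, and 3 x 108 = 324, as stated. No medication count enters it.

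**The case against.** The strongest reply is that no planned comparison is shown to be affected. Medication number is a participant characteristic in Section 4.9. It is absent from the objectives, from the outcomes in Table 2 and from the analyses in Table 3. Appendix B already provides a common collection, and if the counts come from it, neither the Arm 3 update nor the outside lists enter them. That stands, and it makes the point minor and conditional.

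A reader might infer that the counts differ between arms by construction. The documents do not support this: the outside lists depend on permission, and nothing says that the enriched list feeds the counts. Nor do they say that the bias most likely runs against Arm 3. Updating the baseline form points at least as readily to cases (b) or (c) as to case (a). It would also be wrong to call the counts the only quantitative measure of the medication review, because staff also determine whether the recommendations were implemented, and that can be counted. The economic link is thin: Section 6.0 speaks of direct medical costs without naming drug costs.

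The Arm 3 text also mentions a history review at the baseline assessment, which might suggest that it precedes allocation. A step for one arm only still has to follow the assignment.

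Finally, form locking and the choice of source list often belong in an analysis or data-management plan. That would answer a complaint of mere silence. It does not fully answer this one, because the protocol itself prescribes an update of the list on a baseline form in one arm.

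**Conclusion.** The point holds in a limited form. The post-allocation update of the medication list in Arm 3 only is in the text. Bias in the medication counts follows only if the updated list feeds them, and it can then go either way: masked or reversed in (a), exaggerated in (b), and absent for change but present for the 4-month total in (c).

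The size is unknown. The figures above illustrate assumed values of D and u, with equal under-reporting on the common form in all arms. They do not estimate the bias in this trial. What is at stake is a descriptive comparison of medication change, and drug costs if the economic analysis includes them. SPPB, the 400-m walk and N=324 are unaffected. The severity is low. The reason to act is that the remedy is nearly free, while an overwritten baseline cannot be restored.

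**What to change.** Add a sentence to Sections 4.6 and 4.9 to this effect:

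- The medication list recorded before randomisation is kept unaltered.
- The total, started and stopped counts, and drug costs if they are used, are taken in all three arms from the common Appendix B collection, with the same form and procedure at baseline, 4 months and the 6-month call.
- The Arm 3 reconciled list and the implementation follow-up are held as a separate intervention process record and do not feed those counts.

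The cost is that wording and a separate REDCap form. It needs no new data and leaves the medication review as delivered. There is a small downside: the common list is less complete than a reconciled one. Some asymmetry may also remain, because Arm 3 participants may report their medications more fully after the review.

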**FRAILTY REHABILITATION: A COMMUNITY-BASED INTERVENTION TO PROMOTE HEALTHY AGING**

recommendations, via letters, to the participant's family physician and community pharmacist. Research staff will follow up with participants regarding their medication lists to determine whether the medication recommendations were implemented.

**All Arms:**

There is good evidence that indicates that **vitamin D3** supplementation preserves muscle strength and functional ability in high-risk groups such as older adults with frailty and reduces the risk of falls [43,44]. Given that it is a low-cost, logistically easy intervention recommended in the management of frail patients, we have elected to give all arms this treatment (1000 IU/daily) for both ethical (a proven intervention in vulnerable cohorts) and practical reasons (many individuals already taking Vitamin D). Individuals already taking Vitamin D (1000 IU/or greater) will continue with prescribed treatments.

After participants’ involvement in the study, all participants will receive complimentary YMCA memberships for a limited time. Participants, if they wish to, will also be offered free resources and an educational session.

**Figure 1: Study Schema**

[figure not shown]

**4.7. Monitoring Compliance:** The study team is well aware of the barriers encountered with compliance when working with vulnerable older adults, which includes transportation challenges, caregiver burden, medical concerns, indifference, cognitive limitations and poor health [45]. Class attendance will be tracked via YMCA attendance monitoring. Participants will be asked to track weekly adherence to home and group exercises, nutrition (ONS, monthly diet food log, and vitamin D), and falls/adverse events in log-books. Study personnel will conduct monthly check-ins by phone to check-in on adverse events and to assess and assist with challenges pertaining to their intervention. In the GERAS DANCE pilot study for cognitively impaired/pre-frail older adults, we have overcome a number of recruitment challenges and we can apply this learning. For example, YMCA trained volunteers will greet and assist participants to ensure safety on arrival. Furthermore, this group of investigators has extensive experience running such trials and can draw on existing infrastructure and past experiences [e.g., Health TAPESTRY [46]; Cardiovascular Health Awareness Program [47]; Vitamin D and Osteoporosis Study (ViDOS) [48,49]].

**4.8. Trial outcomes:** Primary, secondary, and exploratory outcomes will be assessed at **0 and 4-months**. Healthcare utilization will be tracked (via monthly phone-call by research personnel) during the intervention phase and for an **additional 6-months** following the intervention. The primary outcome measures are the Short Performance Physical Battery (SPPB) [50] and 400m Walk Test [51] (**Table 2**). The **SPPB was the primary outcome of the first frailty intervention trial** [8] and demonstrated improvement in both the FIT study and the LIFE trial, the largest physical activity study in older adults, to date [52,53]. SPPB total scores range from 0-12, and  $\leq 7$  is an established cut-off for poor physical performance. A substantial clinical meaningful change in total SPPB score is 1.3 points [54]. A clinically significant change is considered in the range of 0.05 with 0.10 considered a substantial shift in scores [55].

A blinded assessor with kinesiology/rehabilitation training (with assistance from a GERAS volunteer who will be trained on safety supervision) will perform study outcome assessments at Hamilton Health Science (piloted in our DANCE study). Data, with identifying information removed, will be securely stored in a locked cabinet in the locked research office, at the GERAS Centre at Hamilton Health Sciences. Electronic data will be entered and stored in a **REDCap (Research Electronic Data Capture) database**.

A subset of participants, from all 3 study arms, will be randomly selected to wear the study ActiGraph GT9X Link Accelerometer for the duration of the study. The device will collect raw acceleration data, physical activity intensity, total sleep time, activity bouts, sedentary bouts, sleep efficiency, and energy expenditure, in real time. **Sarcopenia outcomes:** All participants will be screened for sarcopenia at baseline. Physical performance based on the 5-time chair stand test with a score of greater than or equal to 12 seconds is predictive of sarcopenia [56]. Of the 324 participants, up to 75 of them with sarcopenia will undergo additional assessments. Aligned with the 2019 Asian Working Group for Sarcopenia Consensus on Sarcopenia and Treatment we will assess, confirm and grade the severity of sarcopenia at baseline and 4-months. Muscle mass will be assessed with readily available dual-energy x-ray absorptiometry (DXA), and the gold standard magnetic resonance imaging (MRI). Up to 75 participants with sarcopenia will be assessed with DXA (**Table 2**). Due to budget constraints, a subset of up to 36 participants will undergo an MRI scan in addition to DXA. Muscle strength will be assessed as grip strength and chair stand tests. Muscle function will be quantified by gait speed, short physical performance

## FRAILTY REHABILITATION: A COMMUNITY-BASED INTERVENTION TO PROMOTE HEALTHY AGING

battery, timed-up and go, and 400m walk tests. Once the study has reached capacity of participants with sarcopenia, requisitions for DXA and MRI will no longer be provided.

**Table 2: Primary and Secondary Outcomes Measures [See timeline in Appendix B]**

|                    |                                                                                           |                                                                                                                                                                                                                                                                                                                                                                                                                                                                                                                                                                                                                                                                                                                                                                               |
|--------------------|-------------------------------------------------------------------------------------------|-------------------------------------------------------------------------------------------------------------------------------------------------------------------------------------------------------------------------------------------------------------------------------------------------------------------------------------------------------------------------------------------------------------------------------------------------------------------------------------------------------------------------------------------------------------------------------------------------------------------------------------------------------------------------------------------------------------------------------------------------------------------------------|
| Primary     | Physical Function
[Baseline and 4-months]                                       | Short Physical Performance Battery (SPPB)
400-m Walk Test [walking speed, m/s]                                                                                                                                                                                                                                                                                                                                                                                                                                                                                                                                                                                                                                                                                             |
| Secondary   | Functional Abilities
[Baseline and 4-months]                                    | Frailty : Fit-Frailty App
Fear of Falling : Icon Falls Efficacy Scale (ICON-FES)
Fitness : Modified Rating of Perceived Exertion (RPE) scale (post-400m walk test)
Strength : Grip strength with handgrip dynamometer [kg]
Cognition : Montreal Cognitive Assessment (MoCA)
Health-related quality of life : EQ-5D-5L
Life Space Mobility : Life Space Assessment
Activities of Daily Living : Katz ADL and Lawton IADL
Activity and Sleep Patterns : ActiGraph GT9X Link Accelerometer Data
Depression/Mood : Geriatric Depression Scale (GDS-SF)
Nutrition : Mini Nutritional Assessment and SCREEN-8
Functional Mobility : Timed Up and Go (TUG) Test |
|                    | Sarcopenia                                                                         | Sarcopenia screening : 5-Time Chair Stand Test (SPPB)[Baseline and 4-month]
Sarcopenia: SARC-F [Baseline and 4-month]
Muscle Mass : DXA † and MRI* [Baseline and 4-month]
† Additional outcome assessed in up to 75 individuals with sarcopenia
* Additional outcome assessed in up to 36 individuals with sarcopenia                                                                                                                                                                                                                                                                                                                                                                                              |
| Exploratory | Healthcare utilization
[Baseline and 4-months and additional 6-month follow-up] | Number of emergency room visits
Number of hospitalizations & length of stay
Institutionalization (to long-term care)
(measured during intervention phase and 6-months)                                                                                                                                                                                                                                                                                                                                                                                                                                                                                                                                                                                        |

**4.9. Participant Feedback:** We will provide all participants with a participation satisfaction survey designed to facilitate a conversation about individual motivators and barriers to participation and attitudes and behaviours surrounding the frailty rehabilitation program. Participant characteristics that will be collected include age, sex, gender [measured by the Physical Self-Attribute Questionnaire [57], chronic conditions, medication use (medication # [total, started, stopped], 25(OH)D vitamin D level (mmol/L), participation in other programs and sociodemographic descriptors. Adherence will be examined in sub-analyses.

**4.10 Study Staff Process Evaluation:** We will be interviewing at least 4 study staff designed to assist in the evaluation of the intervention processes. The interview will be approximately 30 minutes long.

